### Interventions

#### ACL injury prevention training

The ACL injury prevention training program will be organized into 18 total sessions over 6 consecutive weeks with a frequency of 3 times a week. The duration of each session will be 90 mins, including a 9–10 min active warm-up, and 3 separate 27–30 min sessions of resistance training, technique/plyometric training, and core strength training. All training will be overseen by a licensed athletic trainer with expertise in screening and prevention of ACL injury and amply trained undergraduate research assistants majoring in exercise science, athletic training, and/or biology. At each session, participants will complete the children’s format of the OMNI-Resistance Exercise Scale [36] immediately after finishing each training component.

The training program is based on the collective previous work of the research team and focused on previous studies that have reduced knee injuries in female athletes [7, 37]. Initial development was derived from Hewett et al. [38] and Myer et al. [4] Recommended guidelines were followed when designing the integrated, comprehensive training program [39]. The resistance training component consists of two sessions a week of hip and knee focused strengthening and one session a week of upper body and ankle strengthening. Resistance will be provided by a variety of mediums, including bodyweight, kettlebells, medicine balls, traditional weight machines, and pneumatic resistance [24]. Table 1 details the resistance training exercise progression. Both the plyometric and core strengthening components were adapted from a pilot study reported by Myer et al. [40] Within each technique/plyometric session, training begins with closed chain, body weight exercises that focus on optimal technique, with the expectation that technique translates as exercises are progressed from controlled to ballistic movements. Specific exercise progressions transition from double- to single-leg, sagittal plane to frontal and/or transverse plane, stable to unstable surfaces, and planned to unplanned movements. Table 2 describes the 6-week progression of the technique/plyometric training component. The core strengthening component focuses on improved activation, co-contraction, and strength of the abdominal, low back, proximal hip, and thigh musculature. Exercises use a variety of unstable surfaces, including BOSU® Balance Trainers and therapeutic exercise balls to perturb the body and enhance engagement of the core musculature. Specifics of the core strengthening training progression can be found in Table 3.

**Table 1 Tab1:** Resistance training protocol utilized during ROBUST trial

Exercise	Method of resistance	Week 1	Week 2	Week 3	Week 4	Week 5	Week 6
*Hip and Thigh (2x/week)*							
Bench squat	BW	2 x 12	-	-	-	-	-
Goblet squat	KB	-	2 x 12	2 x 10	2 x 10	2 x 8	2 x 8
Deadlift	AIR	2 x 12	2 x 12	2 x 10	2 x 10	2 x 8	2 x 8
Stationary lunges	BW	2 x 12	2 x 12	-	-	-	-
Walking lunges	BW	-	-	2 x 10	-	-	-
Walking lunges	KB (unilateral resistance)	-	-	-	2 x 10	-	-
Walking lunges	KB (with rotation)	-	-	-	-	2 x 8	-
Walking lunges	KB (unilateral shoulder press)	-	-	-	-	-	2 x 8
Reverse hypers	Weight	2 x 12	2 x 12	2 x 10	2 x 10	2 x 8	2 x 8
Single-leg RDL	BW	2 x 12	-	-	-	-	-
Single-leg RDL	KB	-	2 x 12	2 x 10	-	-	-
Runners	BW	-	-	-	2 x 10	-	-
Runners	KB	-	-	-	-	2 x 8	2 x 8
Band walk	RB (at knees)	2 x 15	-	-	-	-	-
Band walk	RB (at ankles)	-	2 x 15	-	-	-	-
Band walk	RB (at toes)	-	-	2 x 15	-	-	-
X Band monster walk	RB (at shoulders)	-	-	-	2 x 15	-	-
X Band monster walk	RB (W’s)	-	-	-	-	2 x 15	-
X Band monster walk	RB (overhead)	-	-	-	-	-	2 x 15
*Upper Extremity and Ankle (1x/week)*							
Seated cable row	Weight	2 x 12	2 x 12	-	-	-	-
Bent over row	DB	-	-	2 x 10	2 x 10	-	-
Reverse pull-ups	BW	-	-	-	-	2 x 8	2 x 8
Push-ups	BW (wide stance on knees)	2 x 15	-	-	-	-	-
Push-ups	BW (narrow stance on knees)	-	2 x 15	-	-	-	-
Push-ups	BW (wide stance on toes)	-	-	2 x 15	-	-	-
Push-ups	BW (narrow stance on toes)	-	-	-	2 x 15	2 x 15	2 x 15
Shoulder press	KB	2 x 12	2 x 12	2 x 10	2 x 10	2 x 8	2 x 8
Triceps dips	BW	2 x 12	2 x 12	2 x 10	2 x 10	2 x 8	2 x 8
Ankle circuit	RB	2 x 12	2 x 12	2 x 10	2 x 10	2 x 8	2 x 8

*BW* body weight, *KB* kettlebell, *AIR* pneumatic resistance, *RB* resistance band, *RDL* Romanian deadlift

**Table 2 Tab2:** Technique and plyometric training protocol utilized during ROBUST trial (3x/week)

Exercise	Week 1	Week 2	Week 3	Week 4	Week 5	Week 6
Double leg squat	1 x 8	1 x 8	1 x 8	1 x 8	1 x 8	1 x 8
Wall jumps	15 sec	15 sec	15 sec	-	-	-
180^o^ wall jumps	-	-	-	15 sec	15 sec	15 sec
Squat jumps	10 sec	10 sec	15 sec	-	-	-
Squat-tuck jump	-	-	-	10 sec	12 sec	15 sec
Broad jump hold	1 x 8	1 x 8	-	-	-	-
Broad jump-jump-jump-hold	-	-	1 x 6	-	-	-
Broad jump-vertical hold	-	-	-	1 x 6	-	-
Broad jump-vertical reaction	-	-	-	-	1 x 6	-
Broad jump-jump-jump vertical reaction	-	-	-	-	-	1 x 8
Box drop deep hold	1 x 10	1 x 10	-	-	-	-
Box drop vertical	-	-	1 x 10	-	-	-
Box drop broad jump hold	-	-	-	1 x 10	-	-
Box drop 180^o^ vertical hold	-	-	-	-	1 x 8	-
Box drop 180^o^ vertical reaction	-	-	-	-	-	1 x 8
Lateral jump and hold	1 x 8	1 x 8	-	-	-	-
Lateral jumps	-	-	10 sec	-	-	-
Lateral hop and hold	-	-	-	1 x 8	-	-
Lateral hops	-	-	-	-	10 sec	-
X-hops	-	-	-	-	-	6 cycles
Single leg squat	1 x 5	1 x 5	1 x 5	1 x 5	1 x 5	1 x 5
Step-hold	1 x 8	1 x 8	-	-	-	-
Jump-single leg hold	-	-	1 x 8	-	-	-
Hop-hold	-	-	-	1 x 8	-	-
Hop-hop hold	-	-	-	-	1 x 8	-
Crossover-hop-hop-hold	-	-	-	-	-	1 x 10
Single-leg lateral Airex hop-hold	1 x 4	1 x 4	-	-	-	-
Single-leg lateral Bosu hop-hold	-	-	1 x 8	-	-	-
Single-leg lateral Bosu hop-hold with catch	-	-	-	1 x 4	-	-
Single-leg 4-way Bosu hop-hold	-	-	-	-	3 cycles	-
Single-leg 4-way Bosu hop-hold with catch	-	-	-	-	-	20 sec
Single tuck jump-soft landing	1 x 10	1 x 10	-	-	-	-
Double tuck jump	-	-	1 x 6	-	-	-
Repeated tuck jump	-	-	-	10 sec	-	-
Side-to-side barrier tuck jumps	-	-	-	-	10 sec	-
Side-to-side reaction barrier tuck jumps	-	-	-	-	-	10 sec
Lunge jumps	10 sec	10 sec	-	-	-	-
Scissor jumps	-	-	10 sec	-	-	-
Lunge jumps (unilaterally weighted)	-	-	-	10 sec	-	-
Scissor jumps (unilaterally weighted)	-	-	-	-	10 sec	-
Scissor jumps with ball swivel	-	-	-	-	-	1 x 10
Single-leg 90^o^ hop-hold	1 x 8	1 x 8	-	-	-	-
Single-leg 90^o^ Airex hop-hold	-	-	1 x 8	-	-	-
Single-leg 90^o^ Airex hop-hold reaction catch	-	-	-	1 x 8	-	-
Single-leg 180^o^ Airex hop-hold	-	-	-	-	1 x 8	-
Single-leg 180^o^ Airex hop-hold reaction catch	-	-	-	-		1 x 8

**Table 3 Tab3:** Core strength training protocol utilized during ROBUST trial (3x/week)

Exercise	Week 1	Week 2	Week 3	Week 4	Week 5	Week 6
BOSU supermans	1 x 12	1 x 12	-	-	-	-
BOSU supermans with perturbation	-	-	1 x 10	-	-	-
Prone bridge (elbows and knees) hip extension opposite shoulder flexion	-	-	-	1 x 10	-	-
Prone bridge (elbows and toes) hip extension	-	-	-	-	1 x 10	-
Prone bridge (elbows and toes) hip extension opposite shoulder flexion	-	-	-	-	-	1 x 10
BOSU double knee-hold	20 sec	20 sec	-	-	-	-
BOSU single knee-hold	-	-	20 sec	-	-	-
Swiss ball double knee-hold	-	-	-	20 sec	-	-
Swiss ball double knee-hold with perturbation	-	-	-	-	20 sec	-
Swiss ball double knee-hold with catch	-	-	-	-	-	20 sec
BOSU double leg pelvic bridges	1 x 10	1 x 10	-	-	-	-
BOSU single leg pelvic bridges	-	-	1 x 10	1 x 10	-	-
BOSU single leg pelvic bridges with ball hold	-	-	-	-	1 x 10	-
Supine swiss ball hamstrings curl	-	-	-	-	-	1 x 10
BOSU lateral crunch	1 x 10	1 x 10	-	-	-	-
Box lateral crunch	-	-	1 x 10	-	-	-
BOSU lateral crunch with catch	-	-	-	1 x 8	-	-
Swiss ball lateral crunch	-	-	-	-	1 x 15	-
Swiss ball lateral crunch with catch	-	-	-	-	-	1 x 8
Box double crunch	1 x 15	1 x 15	-	-	-	-
Box swivel double crunch	-	-	1 x 15	-	-	-
BOSU swivel ball touches (feet up)	-	-	-	1 x 15	-	-
BOSU double crunch	-	-	-	-	1 x 15	-
BOSU swivel double crunch	-	-	-	-	-	1 x 15
Swiss ball back hyperextensions	1 x 15	1 x 15	-	-	-	-
Swiss ball back hyperextensions and reach	-	-	1 x 15	-	-	-
Swiss ball back hyperextensions with back fly	-	-	-	1 x 15	-	-
Swiss ball back hyperextensions with reach lateral	-	-	-	-	1 x 15	-
Swiss ball back hyperextensions with lateral catch	-	-	-	-	-	1 x 15
Russian hamstrings curl	1 x 10	1 x 10	1 x 10	1 x 10	1 x 10	-
Swivel Russian hamstrings curl	-	-	-	-	-	1 x 10

### ROBUST

Subjects will participate in a biofeedback session (10 min) once weekly over the course of the training program. A three-dimensional motion analysis system, consisting of fourteen digital high-resolution cameras (Raptor-12, Motion Analysis Corporation, Santa Rosa, CA), and two time-synchronized, embedded, oversized force platforms (AMTI, Watertown, MA) will be used to provide biofeedback for participants. For each ROBUST session, participants will be instrumented with retroreflective markers bilaterally on their medial and lateral malleoli, medial and lateral knee joint line, ASIS, greater trochanter, and the sacrum and left PSIS to define the ankle (centroid method), knee (centroid method) and hip joint centers (Bell method) respectively. Additionally, rigid 4-marker clusters will be affixed bilaterally to each participant’s lateral thigh and shank with cohesive tape (Pro-Trainer® cohesive tape, Medco Sports Medicine^TM^, Tonawanda, NY) and four individual markers will be placed on the foot (toe, anterior lateral foot, posterior lateral foot, heel) with double-sided tape for tracking purposes. After instrumentation, a static trial will be collected of the participant in anatomical position to model the segment coordinate system and define each tracking maker. The static model will be defined directly in Visual3D with the model used directly during real-time biofeedback.

For ROBUST training, each participant will be in front of a 95 ft^2^ screen which will depict a real-time avatar and graph of either hip extensor moment (hip-focused group), knee abduction moment (knee-focused group), or knee flexion angle (sham group) with a highlighted goal region that they are encouraged to attain (Fig. 2). At each session, participants will perform a series of 3 exercises (Table 4) including a double-leg squat, single-leg squat, and single-leg jump landing. Although encouraged to focus on the visual biofeedback data, participants will receive verbal instructions and feedback from a member of the research team. Members of the hip-focused group will be instructed to activate posterior-chain muscles throughout the movements in order to increase the hip extensor moment feedback. The knee-focused group will be instructed to maintain knees over toes while pushing laterally through their feet. Participants that receive sham biofeedback are instructed to bend the knees while squatting.

**Fig. 2 Fig2:**
[figure not shown]
Sample participant during biofeedback training

**Table 4 Tab4:** Exercises performed during ROBUST biofeedback sessions

Weeks 1 -2	Week 3	Week 4	Week 5	Week 6
Double leg squat (DLS)	DLS arms front	DLS arms chest	DLS arms up	DLS deep
Single leg squat (SLS)	SLS arms front	SLS arms chest	SLS arms up	SLS deep
Step hold	Jump single leg hold	Hop hold	Hop hop hold	Crossover hop hop hold

### Outcome measures

At the pre-testing session, all participants will complete an electronic RedCap (Research Electronic Data Capture) [41] survey detailing their 1) demographic information, 2) sport participation history, 3) lower extremity and spine injury history, 4) parental heights for calculation of pubertal stage, and 5) menstrual history.

The primary outcome variables of interest for this study will include lower extremity biomechanics during double- and single-leg jump landing and unplanned cutting tasks. Participants will perform these tasks on a synthetic turf (TurfLink TL80), while wearing standardized cleats (adidas x15.2; Beaverton, Oregon, USA). Each participant will be instrumented for 3-dimensional biomechanical analysis with 43 retroreflective markers placed on the sternum, sacrum, left posterior superior iliac spine, C7, 3 points on the upper back (via a thin backpack), and bilaterally on the shoulder, upper arm, elbow, wrist, anterior superior iliac spine, greater trochanter, midthigh, medial and lateral knee joint line, tibial tubercle, midshank, distal shank, medial and lateral malleolus, and to the foot at the heel, dorsal surface of the lateral midfoot, lateral rear foot and toe via double-sided tape. A static trial will be collected to determine each subject’s neutral alignment and anatomically define each body segment, by which subsequent biomechanical measures will be referenced. Using Cortex software (version 5; Motion Analysis Corp, Santa Rosa, California, USA) three-dimensional motion capture will be sampled at 200 Hz and kinetic data will be sampled at 1200 Hz with the system previously described.

### Landing biomechanics

Each participant will perform three trials of a drop vertical jump (DVJ) (Fig. 3a). Participants will start on top of a 31-cm box, with their feet positioned 35-cm apart and arms at their side. A member of the research team will instruct them to drop down directly off the box, land on both feet at the same time and immediately perform a maximal vertical jump, reaching for an overhead target that was previously placed at their maximal vertical countermovement jump reach.

**Fig. 3 Fig3:**
[figure not shown]
Knee abduction moments during (**a**) double-leg landings, (**b**) single-leg landings, and (**c**) unanticipated cutting will be the primary outcome measures

Participants will then perform three trials of a single-leg landing (Fig. 3b) on each limb in a previously randomized order, and the order will be identical for post- and 6 month retention testing sessions. A meter stick will be placed adjacent to the landing area, beginning at a target placed in the center of the force plate. A starting line will be placed on the meter stick at 40% of the subject’s height. A 5-inch hurdle will be placed midway between the starting line and landing target. Participants will be instructed to stand on one leg with their toe at the starting line. They will then hop forward over the hurdle on one leg, land on the same leg and hold the landing for 2 s without allowing the non-stance limb to touch the ground or come in contact with the stance limb. An inability to hold the landing for 2 s will result in repeating the trial.

### Cutting biomechanics

For the unplanned cutting task, each participant will complete 3 successful trials of a 90° sidestep cut and backpedal cut on each limb, with the order of cuts and backpedals randomized for each limb (Fig. 3c). Prior to beginning the trial, participants are made aware of which limb they will be cutting or backpedaling off. For example, if the right limb is the limb of interest, participants will either plant on their right limb and cut 90° to the left or make initial contact with their right limb to decelerate and backpedal. Participants will start 5 m away from the force plates and be instructed to run forward at 75% of their maximal speed. A trigger will be placed 2 m in front of the force plate that, when passed, will immediately illuminate a light (FITLIGHT trainers™, FITLIGHT Sports Corp., Aurora, Ontario, Canada) placed 1.5 m behind the force plate telling the athlete to cut (light placed at waist level towards the cutting direction) or backpedal (light placed at eye level directly behind of the force plates). As stated, speed will be self-selected, though participants will be encouraged to maintain 75% of their maximal speed, and the speed of each trial will be measured using two timing gates (TracTronix, Lenexa, Kansas, USA), placed 2.5 m apart, with the latter gate 0.45 m from the front edge of the force plate. Trials will be repeated if the participant cuts or backpedals off the wrong limb, or does not get their plant limb fully on to the force plate when cutting.

### Secondary outcome measures

Isokinetic hip extensor strength will be tested using an isokinetic dynamometer (HUMAC/NORM Testing and Rehabilitation System, Computer Sports Medicine Inc. Stoughton, Massachusetts, USA) at a speed of 60° per second (Fig. 4). Participants will be placed in the prone position with their anterior inferior iliac spines on the table, their hip and knee flexed to 90°, and their greater trochanter aligned with the rotational axis of the dynamometer. A stabilization strap will be placed over the pelvis to ensure that the participant’s hips stay on the table throughout the trials. The resistance pad of the dynamometer will be positioned at the distal thigh, just proximal to the popliteal fossa. To un-weight the contralateral limb, a box will be placed underneath the knee of the contralateral limb for the participant to rest with their hip flexed to 90°. Both concentric and eccentric hip extensor strength will be measured between 90 and 30° of hip range of motion in conjunction with verbal encouragement from the tester. Each participant will complete 3 practice repetitions prior to completing 5 maximal effort repetitions for each condition. The limb and contraction condition (eccentric or concentric) will be randomized for each participant. Peak torque and work per repetition will be calculated for the second, third, and fourth repetitions.

**Fig. 4 Fig4:**
[figure not shown]
Participants’ isokinetic concentric and eccentric hip extensor strength will be tested at pre-, post-, and retention testing sessions

Double-leg vertical and single-leg horizontal jump performance will be measured during a countermovement jump (CMJ) and single-leg hop for distance, respectively. CMJ height will be captured during biomechanical testing with the 3D motion capture system on the synthetic turf surface. Participants will complete three maximal effort trials while reaching their hands vertically towards an overhead target that was placed at the tips of the fingers during 2–3 CMJ practice trials. Jump height will be calculated as the difference between the peak vertical displacement of the center of mass and the position of the center of mass during static standing. Participants will also complete three trials of a single-leg hop for distance on each limb while wearing a standardized sneaker (adidas adipure 360.2, Portland, OR, USA) on a rubber gym floor. While standing on one leg with their toes behind the starting line, participants will leap forward as far as possible, landing on the same limb and holding the landing for 2 s. The researcher will measure the distance from the starting line to the distance of the toe using a tape measure affixed to the floor. Trials will be repeated if the participant is unable to hold the landing for 2 s and/or touches the ground or the hopping leg with the opposing limb.

Quickness and change of direction performance will be measured during three trials of the pro-agility drill [42]. Participants will stand in the middle of a single timing gate (SMARTSPEED™, Fusion Sport Inc., Australia) placed in the center of a court surface. When the light on the timing gate flashes green, participants are instructed to turn and sprint in one direction (self-selected) to a piece of tape on the floor 4.57 m away, turn and sprint 9.14 m in the opposite direction to another piece of tape on the floor, turn and sprint 4.57 m until they pass through the timing gate. The total time to complete the trial will be recorded for analysis.

Core muscle strength will be assessed using the sports-specific core muscle test as previously described by Tong et al. [43] Participants will begin in a standard prone plank position on their forearms and toes, while attempting to hold for one minute. If able, participants will subsequently transition through the following stages of a prone plank 1) lifting right arm off the ground and holding straight ahead for 15 s, 2) lifting left arm off the ground and holding straight ahead for 15 s, 3) lifting right leg off the ground for 15 s, 4) lifting left leg off the floor for 15 s, 5) lifting both right arm and left leg off the floor for 15 s, 6) lifting left arm and right leg off the floor for 15 s, 7) standard prone plank for 30 s, 8) repeating progression from step 1 above. Participants will complete one trial of this test, which is measured in total time by the researcher with a standard stop watch. Trials will be stopped if participants cannot maintain a proper plank position (i.e. hip elevation, drop, or shift) following a maximum of 3 verbal corrections in each stage or if a body part other than the participants’ forearms and toes makes contact with the ground.

### Retention testing

After completing the 6-week training program and post-test assessment, participants will provide monthly sport participation, athletic exposure, and injury history data. An electronic survey will be emailed to the participants and their families to help with accurate data collection and retention efforts. Participants will return to the Human Biomechanics and Physiology Laboratory 6 months after training, utilizing the same researchers and baseline methodology.

### Data and statistical analysis

Intention-to-treat (ITT) analysis will be performed according to CONSORT statement guidelines [44]. Baseline differences between groups will be analyzed using an analysis of variance (ANOVA). Improvement in the biomechanical outcomes of knee load and hip-strategy will be assessed using Paired-*T* test (when normal) or Signed Wilcoxon rank-sum test (when non-normal) for each study arm. An ANOVA will be used to compare the improvement in post- vs. pre-training in knee load and the hip-strategies across the three study arms. Tukey’s multiple comparison procedures will be used to adjust for multiple comparisons. ANOVA analyses will consider adjusting for age and other baseline covariates as determined earlier. All ITT participants will be analyzed. Further, we will adopt multivariate ANOVA techniques, which will be modeling the study outcome measures as a whole in testing study hypotheses.

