### Participants

One hundred fifty female soccer players between the ages of 9 and 19 will be recruited from local soccer clubs and high schools for this study. Recruitment will be performed primarily through discussions with club presidents, athletic directors, directors of coaching, coaches, and parents. The study sample will consist solely of female youth soccer players that participate on a competitive team at the time of enrollment. Participants will be excluded if they are not currently able to participate in sport due to an injury or cannot commit to participating in the 6-week intervention.

An equal sample size of *N* = 50 will be randomized to each of the three study arms. Assuming 20% of loss to follow up, a sample size of 40 is expected in each group at the conclusion of the study. Under this assumption, it was estimated that one-way analyses of variance will have 80% of power to detect at the 0.05 level a difference in means characterized by a variance of means of 0.082 (i.e. the averaged group mean deviations from the grand mean being 0.082 or higher of the common standard deviation). Previous results suggest an improvement in knee abduction load between two forms of biofeedback training with estimated mean+/-SD of 11+/-6 Nm vs. 2+/-10 Nm, indicating sufficient statistical power in this study [35].

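### The between-arm ANOVA of change scores leaves the baseline value out of the fixed model; pre-specified ANCOVA would be more precise, by an amount that depends on an unstated pre-post correlation

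*Protocol article*

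**What the plan says.** All the relevant statements on method are in the protocol article, Data and statistical analysis.

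- The between-arm comparison uses change scores: "An ANOVA will be used to compare the improvement in post- vs. pre-training in knee load and the hip-strategies across the three study arms".
- Pairwise comparisons are covered: "Tukey’s multiple comparison procedures will be used to adjust for multiple comparisons".
- Adjustment is left open: "ANOVA analyses will consider adjusting for age and other baseline covariates as determined earlier". Age is the only covariate named.
- The randomized arms are tested against each other at baseline: "Baseline differences between groups will be analyzed using an analysis of variance (ANOVA").

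The Participants section sizes the trial for a one-way ANOVA with "80% of power to detect at the 0.05 level a difference in means characterized by a variance of means of 0.082", on 40 evaluable participants per arm. Under Randomization, allocation follows the pre-test, so the pre-test knee abduction moment is a true baseline covariate. It is measured in every randomized participant.

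**The concern.** A change score subtracts the whole baseline value, whatever the correlation between baseline and follow-up. ANCOVA estimates how much of the baseline to remove, so its residual variance is never larger. Under randomization the two methods target the same difference between arms, so what is at stake is precision. That applies to every between-arm contrast, including hip-focused against knee-focused feedback, which the Hypotheses section singles out for unplanned cutting.

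The model is also not fixed. The covariate sentence says adjustment will be considered, and it refers back to covariates already determined, but the article gives no such list. The only earlier step in the section that could supply one is the baseline ANOVA. In a randomized trial that test examines a null hypothesis that holds by design. It does not show whether a covariate is related to the outcome.

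**Working it through.** **Inputs from the article (Participants).** Three arms; 50 randomized and 40 evaluable per arm; alpha 0.05; variance of means 0.082 in units of the common variance; stated power 80%. Prior improvements of 11 (SD 6) and 2 (SD 10) Nm.

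**Input not in the article.** The pre-post correlation r and the separate pre and post SDs of knee abduction moment. I take r from 0.3 to 0.9 as an assumption, first with equal SDs and then with unequal SDs.

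**Step 1: the stated power.** N = 3 × 40 = 120, and the noncentrality is 120 × 0.082 = 9.84. The noncentral F distribution with 2 and 117 degrees of freedom gives power 79.8%, so the stated 80% reproduces.

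**Step 2: ANCOVA against change scores, equal SDs.** Let s² be the common variance at each visit.

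- Change score: 2s²(1-r)
- ANCOVA residual: s²(1-r²)
- Ratio: (1-r²) / [2(1-r)] = (1+r)/2, so the saving is (1-r)/2

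Power is recomputed with noncentrality 9.84 / [(1+r)/2] and 2 and 116 degrees of freedom, one degree being spent on the baseline covariate.

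| Assumed r | Variance saving | Omnibus power, 40 per arm | Evaluable n per arm for 80% |
|---|---|---|---|
| 0.3 | 35% | 94.0% | 27 |
| 0.5 | 25% | 90.3% | 31 |
| 0.7 | 15% | 86.2% | 35 |
| 0.9 | 5% | 81.9% | 39 |

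The variance ratio also applies to each pairwise contrast. The power column applies only to the omnibus test.

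**Step 3: unequal SDs.** Let k be the post/pre SD ratio. In units of the pre-test variance, the change-score variance is 1 + k² - 2rk and the ANCOVA variance is k²(1-r²). The difference is (1-rk)², which is never negative.

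- k = 1.2, r = 0.5: 1.08 / 1.24 = 0.871, saving 13%
- k = 1.2, r = 0.7: 0.734 / 0.760 = 0.966, saving 3%
- k = 0.8, r = 0.5: 0.480 / 0.840 = 0.571, saving 43%
- k = 0.8, r = 0.7: 0.326 / 0.520 = 0.628, saving 37%

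**Step 4: the cited prior effect.** Pooled SD = √[(36 + 100)/2] = 8.25 Nm, so the standardized difference is 9 / 8.25 = 1.09. At 40 per arm, omnibus power is above 99% whether the third arm's mean is 2, 6.5 or 11 Nm. At an effect that large, ANCOVA adds almost nothing to power.

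**The case against.** The strongest reply is that nothing here is an error. Under randomization, an ANOVA of change scores is unbiased and has a valid type I error. The sample size was calculated for that kind of analysis, and the stated power reproduces. All of this stands. A reader might infer that regression to the mean biases the planned comparison. It does not do so over the randomization. Chance baseline imbalance affects the single realized estimate, and that is a matter of precision.

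A reader might also infer that covariates will be picked by baseline p-values. The text does not say this. Age is named without reference to any test, and covariates determined earlier could mean covariates fixed in advance. The inference rests only on the baseline ANOVA being the sole earlier step in the section.

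Nor does the article rule out a baseline adjustment, since other baseline covariates could include the pre-test value. A change score adjusted for its own baseline gives the same between-arm estimate and residual variance as ANCOVA on the post-test value. The plan therefore permits the better model but does not commit to it, and the savings above are measured against the unadjusted analysis.

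A full covariate list may properly sit in an SAP that is not shown, and its absence is no fault. What remains is what the article does state: a change-score ANOVA, optional adjustment and a baseline significance test.

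Finally, the cited prior effect makes power look ample. However, the Discussion describes that study as kinetic against kinematic feedback, and both the hip-focused and the knee-focused arms receive kinetic feedback. The prior effect therefore does not establish ample power for the contrast between those two arms.

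**Conclusion.** The point holds as an avoidable loss of efficiency in a model left open. It is not a bias, an invalid test or a shortfall against the stated power.

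With equal SDs, the variance saving is 5% to 35% for r from 0.9 down to 0.3, and omnibus power at the planning effect is 82% to 94% instead of 80%. For r = 0.5 to 0.7, the saving is 15% to 25% with equal SDs, 3% to 13% if the post/pre SD ratio is 1.2, and 37% to 43% if it is 0.8. It is tempting to quote one of these ranges as the gain for this trial. The article does not support that, because it gives neither r nor the separate SDs. The direction is firm apart from the small cost in degrees of freedom; the size is not known. The gain in power matters mainly for effects near the planning value, not for one as large as the cited prior result.

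**What to change.** Replace the between-arm ANOVA sentence and the covariate sentence with the following:

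> Post-training knee abduction moment for each task, and each hip-strategy measure, will be compared across arms by ANCOVA with arm, the pre-test value of the same measure, and age as pre-specified covariates, with Tukey adjustment of the pairwise contrasts.

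This removes both the wording that makes adjustment optional and the reference back to an unstated list. Report baseline characteristics by arm descriptively, without significance tests.

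The cost is wording and one degree of freedom per added covariate. No new data are needed: the pre-test measures are taken before randomization, and demographic information is collected at the same session. The sample size can stay as it is, with any gain taken as extra precision.
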